### 13.3 Stopping Rules

If at any time during the study, the investigators, mentors, or IRBs judge that the risk to subjects outweighs the potential benefits, they shall have the discretion and responsibility to recommend that the study be terminated. We do not, however, have a pre-specified stopping rule.

## 14 Data Handling and Record Keeping

### 14.1 Confidentiality

As indicated in our research plan, we will do our best to protect participant data in accordance with national confidentiality laws. Participants may be at risk if they reveal a mental disorder in the discussion and their data is leaked (e.g., the social consequences of having a stigmatized disorder). For this reason, we have drawn up strict guidelines on protecting participant confidentiality. All cases of social harm and other adverse events will be brought to the attention of the mentors and the Principal Investigator. Cases of social harm that are determined to be UP, unexpected and serious (or could pose increased risk to subjects), and possibly related to being in the research will be reported to the BMC IRB, the Universidad del Pacífico, and the National Instituted of Health.

Participants will be assigned a unique study ID, with study data associated only with these IDs. Participants will be identified in all study materials solely by participant number, visit number, and visit date. A master list of participants' names and study IDs will be kept in a locked filing cabinet separate from other data. The principal investigator and research study coordinators will be the only individuals with access to this list. The master list will be destroyed at the end of the study. Transcriptions for the assessment of fidelity will use participant numbers, not their names. By recording study data in this manner, the information can be considered "de-identified," thus complying with the Health Insurance Portability and Accountability Act (HIPAA) Privacy Rule standards for individually identifiable health information.

Only the research staff will have access to participants' identifiable private information. No additional contact or data collection will be undertaken for the proposed research. All data is

Adaptation and assessment of a common element treatment protocol designed to improve mental health in forcibly displaced populations  
obtained specifically for research purposes.

Version 1, September 17, 2024

All audio recordings, transcripts, notes, and completed qualitative assessments will be stored in a locked filing cabinet and kept in restricted areas. All USB drives and computers will be encrypted and password protected. Electronic versions of audio recordings, transcripts, notes, and quantitative data will be password protected. Passwords will change periodically and will only be accessible to specified research staff. All digital audio recordings will be uploaded to the studio computer immediately after recording and the audio file will be deleted from the digital recorder.

This study will be registered at ClinicalTrials.gov.

#### 14.2 Study Documentation, Source Data, and Case Report Forms (CRFs)

Data on eligibility, the participant screening, demographic information, outcome measures (PHQ9, GAD7, LEC5 and PCL5), potential moderator variables (IPL), adherence and acceptability will be entered directly into the electronic system REDCap. Data on feasibility (recruitment and retention) will be entered into an Excel sheet. All the data will be generated by the study procedures and will meet the ALCOA-C criteria.

See Appendix for the forms to be used in REDCap.

Corrections on data collection forms: If any entry error has been made to hardcopy data collection forms, to correct such an error, a single straight line will be drawn through the incorrect entry and the correct data will be entered above it. All such changes will be initialed and dated. There will be no erasures or white-out on CRFs. For clarification of illegible or uncertain entries, the clarification will be printed above the item, then initialed and dated.

See the Appendix for the following CRFs:

- Demographics Screening
- Psychosis Questions
- PHQ9
- GAD7
- LEC5
- PCL5 (monthly)
- PCL5 (two-week version)
- IPL
- Acceptability

Data forms will undergo a systematic and rigorous editing process prior to being keyed into the database. The research coordinator ([name], at the subcontract cite Universidad del Pacífico) and PI will routinely evaluate the data and discuss any problems and questions with the investigator team at the regular weekly team meetings. Data management reports across the three following domains will be employed: entered, verified, and edited. These reports of data records will be evaluated once a month. To help ensure data protection, backup copies will be generated each week. Additionally, our hard copy record systems, as described previously, will be maintained in fire-resistant locked cabinets at each site. Data collected in Perú from study assessments, will be will be available for the PI and research staff REDCap. In addition, data on interventionist training, independent assessor training, clinical supervision, and participant progress through the study procedures will also be entered and uploaded. This data entry will occur as close to real time as possible to facilitate data management and monitoring of study operations.

Adaptation and assessment of a common element treatment protocol designed to improve mental health in forcibly displaced populations

Version 1, September 17, 2024

All audio recordings, transcripts, notes and completed quantitative assessments will be stored in a locked file cabinet and kept in restricted areas. All USB flash drives and computers will be password protected and encrypted. Electronic versions of audio recordings, transcripts, notes, and quantitative data will be password protected. Passwords will be changed periodically and only accessible to specified research staff. All digital audio and video recordings will be uploaded to the study computer immediately following recording and the audio file will be deleted from the digital recorder.

Computer files with participant information will be available for PI and research staff at REDCap, a password-protected computer software and website that is compliant with the Health Insurance Portability Act of 1996 (HIPAA) and is used by BMC to transmit confidential clinical and research files. Only the research team, including the PI and the mentoring team, will have access to the data. Recordings will be maintained until seven years after the publication of study results in line with the guidelines of the American Psychiatric Association.

Participants will be assigned a unique study ID, and study data will be associated with participants' study IDs only. Participants will be identified on all study materials only by participant number, visit number, and date of visit. A master list of participant names and their study IDs will be stored in REDCap separate from the rest of the data. The study research coordinators, and the PI will be the only people with access to this list. The master list will be destroyed upon completion of the study. Participants' names will not be used in recorded interviews. By recording the study data in this manner, the information can be considered 'de-identified,' and therefore, compliant with the Standards for Privacy of Individually Identifiable Health Information (Privacy Rule) of HIPAA.

### 14.3 Study Records Retention

Study records, screening consent and participation consent forms and the data collected during the study will be retained for 7 years after the study is closed and then destroyed. They will be preserved in electronic form.

## 15 Statistical Plan

### 15.1 Study Hypotheses

We expect to see a trend toward less depression, anxiety and PTSD over time in the intervention group in comparison to the waitlist control group. Experiences in migration, integration and demographic variables may moderate the efficacy of the intervention.

### 15.2 Sample Size Determination

The sample comprises  $n = 90$  pilot participants, of which  $n = 60$  will be randomly assigned to the intervention group and  $n = 30$  to a waitlist control. The sample size for pilot participants is based on a method outlined by Viechtbauer. Viechtbauer suggests that for a pilot trial a sample size of  $n = 59$  is sufficient to detect a problem that emerges for 5% of participants.

We expect participant recruitment to be feasible as the PI and colleagues at Universidad del Pacifico have recruited and engaged with over 2,000 research participants in mental health research. For example, for the prior stages of this project we have engaged  $n = 19$  experts and  $n = 29$  migrants.

### 15.3 Statistical Methods

All analyses will be performed using multiple packages within SPSS and R. Descriptive statistics will be calculated with frequencies and percentages or means and standard deviations. Demographic variables will be tested for differences in distribution with bi-variate analyses. Variable distributions will be examined, and transformations made, when distributions are skewed or otherwise violate parametric analytic assumptions. All reasons for missing data will be tabulated by reason and reported. All quantitative outcomes will be tested at two-sided  $\alpha=.05$  level. Regression analysis will examine changes in primary outcomes in depression, anxiety and post-traumatic stress disorder symptoms and feasibility and acceptability in recruitment rate, assessment completion rate, attendance rate and acceptability rated by providers and participants. Regression will plot the trends in outcome variables over the three study periods (baseline, post-intervention and 6 months following). We will also explore the relationship between covariates and baseline outcome scores and retention, fidelity, and satisfaction to identify any characteristics that might be associated with implementation success. All analyses will adjust for sex as a covariate and it will be tested as an effect modifier (e.g. stratification).

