| Design/Methodology:             | 
Migrants will be randomized to receive the intervention (<math>n = 60</math>) or wait list control (<math>n = 30</math>). Mental health outcomes (PHQ9, GAD7, PCL5) will be assessed at baseline during screening, throughout the intervention, post treatment, and at 1-, 3-, and 6- months follow-up. Demographic information, the IPL will be assessed at the time of enrollment. LEC5 will be assessed at baseline and at 1-, 3- and 6-month follow-up. Acceptability will be assessed after each session. All assessments will be conducted by the research team through a secure link in REDCap. Each migrant will participate in 5 assessment sessions and 6-12 intervention sessions with prior assessment of mental health outcomes. The intervention sessions have a frequency of once a week. In the case of the waitlist control, mental health outcomes will be assessed at baseline at the time of enrollment and at endline 12 weeks after baseline. Once the endline has been assessed, they will receive the intervention, with corresponding assessments as described previously. In the case of the providers, feasibility and acceptability will be assessed after each session. See Appendix for a graph of the design, schedule and assessments.
 |

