### 3.2 Rationale and Purpose

If we consider the pressing need for mental health support of the Venezuelan population in Peru, the role of community organizations and NGOs in providing mental health services, and the urgency for capacity building in the growing primary and secondary level of attention of the formal mental health system, the importance of identifying best practices and designing culturally and contextually appropriate interventions becomes clear. The purpose of this study is to test the efficacy of such an intervention. Previous phases of this study have gathered information via interviews with migrants and experts on relevant cultural and contextual aspects that need to be taken into consideration, when adapting a mental health intervention for the specific population of Venezuelan migrants living in Peru. Alongside these considerations, CBT strategies to treat CMD, that have proven effective in similar populations and that were implemented by lay providers, have been identified. On this basis, strategies have been selected, adapted and presented to experts working in the provision of mental health services, as well as to migrants. Some modifications have been undertaken based in their feedback, resulting in the intervention to be tested in the study described here. Of note, we know of no study to date which has proven the efficacy of an intervention with the characteristics: a) aimed at treating CMD such as anxiety, depression and PTSD; b) provided by lay providers; and c) specifically tailored for Venezuelan migrants established in Lima. Since there is no standard care provided to Venezuelan migrants suffering from CMD, we have opted for a waitlist control study design. As a hypothesis we expect to see a trend toward less depression, anxiety and PTSD over time in the intervention group. Experiences in migration, integration and demographic variables may moderate the efficacy of the intervention.

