## 5 Study Design

This is a randomized pilot study with waitlist control with the aim to compare trends in outcomes between the intervention and control group. Following the intent-to-treat principle, all randomized subjects will be included in the analyses. The sample size for pilot participants is based on a simple method outlined by Viechtbauer, which suggests a sample size of  $n = 60$  will be adequate for problem detection. As no treatment exists for forcibly displaced populations, we will randomize  $n = 30$  to waitlist control and treat all participants. The randomization process to intervention or waitlist control will be carried out by a random number generator. Participant with odd numbers will be assigned to the active treatment group and participants with even numbers to the waitlist control group.

The study population comprises outpatient participants, with symptoms of common mental health disorders such as anxiety, depression and/or PTSD (inclusion criteria are described in detail in section 5), adult ( $\geq 18$  years old), male and female, of Venezuelan nationality, that

Adaptation and assessment of a common element treatment protocol designed to improve mental health in forcibly displaced populations  
Version 1, September 17, 2024  
have arrived in Lima in years 2014 to the present.

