## 12 Study Procedures

See the Appendix for the schedule of events.

| Phase       | Time                                                                                                         | Description                                                                                                                                                                                                                                                                                                                                                      |
|-------------|--------------------------------------------------------------------------------------------------------------|------------------------------------------------------------------------------------------------------------------------------------------------------------------------------------------------------------------------------------------------------------------------------------------------------------------------------------------------------------------|
| Recruitment | 
Begin: January 2025
 
End: When n = 90 is reached (n = 60 intervention; n = 30 waitlist control)
 | 
Opt-in: Potential participants learn about the study and contact the research team. Information is shared via
 
 
• Posters in the front of organizations NGOs active in migration, health centers and community mental health centers, shelters, schools
 
• Flyers available at these institutions
 
 |

|                                                          |                                                                                                                                                                      |                                                                                                                                                                                                                                                                                                                                                                                                                                                                                                                                                                                                            |

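### Section 15.3 runs the trend regression to 6 months and does not confine the between-arm test to baseline and week 12, the only period with an untreated control

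*Protocol*

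**What the plan says.** Section 15.1 expects less depression, anxiety and PTSD "over time in the intervention group in comparison to the waitlist control group". Section 5 describes a randomised pilot "with the aim to compare trends in outcomes between the intervention and control group". Both are between-arm statements.

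The waitlist arm has two untreated assessments. The Protocol Summary says its "mental health outcomes will be assessed at baseline at the time of enrollment and at endline 12 weeks after baseline", and then: "Once the endline has been assessed, they will receive the intervention, with corresponding assessments as described previously".

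Section 15.3 states the analysis: "Regression will plot the trends in outcome variables over the three study periods (baseline, post-intervention and 6 months following". It names no arm, no waitlist and no 12-week contrast. The same section adds: "All quantitative outcomes will be tested at two-sided" 0.05.

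Section 3.2 words the expectation without the comparator: "we expect to see a trend toward less depression, anxiety and PTSD over time in the intervention group". Section 4.1 gives a similar expectation and names no group.

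**The concern.** After week 12 the waitlist receives the same intervention. Any arm contrast at the last period is therefore treated against treated, and its expected value is near zero even if the intervention works. A trend fitted across all three periods mixes the informative interval with one where no arm difference is expected.

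The label for the second period is also unclear for the waitlist. Its only untreated follow-up, the week-12 endline, comes before its intervention. Read literally, its post-intervention value is taken after its own treatment, and the untreated value drops out of the stated analysis.

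The remaining reading, change over time within the treated arm, is uncontrolled. Participants enter because they score high at screening, and that screening score is also the baseline. Some fall is expected with no treatment effect.

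At stake is the primary objective, which section 4.1 states as efficacy. A working intervention could look inert, or natural recovery could be credited to it.

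**Working it through.** **The plan's own figure.** Section 15.2 gives n = 59 to detect a problem affecting 5% of participants. With 95% confidence (assumed, since the section does not state it), n = ln(0.05)/ln(0.95) = 58.4, rounded up to 59. It reproduces. It is a problem-detection size and says nothing about power for an arm comparison.

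**Inputs for the slope check.** From the protocol: 60 intervention and 30 waitlist; waitlist untreated at baseline and week 12 only; last period 6 months after treatment or endline. Assumed: the effect d appears by the end of treatment and is maintained, there is no change without treatment, and one straight line is fitted per arm. Expected means are then 0, -d, -d (intervention) and 0, 0, -d (waitlist, with week 12 as its second period).

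**Slopes.** Slope = sum of (t - mean t) × y, divided by the sum of (t - mean t)².

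- Periods 0, 1, 2: deviations -1, 0, 1; divisor 2. Intervention -d/2, waitlist -d/2. Difference 0.
- Months 0, 3, 9 in both arms: mean 4; deviations -4, -1, 5; divisor 16 + 1 + 25 = 42. Intervention (d - 5d)/42 = -4d/42 = -0.095d. Waitlist -5d/42 = -0.119d. The difference is d/42 per month, with the waitlist appearing to improve faster.
- Waitlist's last point at month 12 (3 months waiting, 3 of treatment, 6 of follow-up): mean 5; deviations -5, -2, 7; divisor 25 + 4 + 49 = 78. Waitlist -7d/78 = -0.090d, against -0.095d. Difference about 0.005d per month in the right direction, which is negligible.
- Both arms aligned to their own treatment: means 0, -d, -d in each. Difference 0 by construction.
- Baseline to week 12 only: change -d against 0. The full effect d is recovered.

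**Rejection rates** (simulation, 5,000 runs, 60 against 30, within-person correlation 0.5, no dropout, two-sided 0.05):

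| Contrast | d = 0.5 SD | d = 0.8 SD |
|---|---|---|
| Slope, periods 0, 1, 2 | 4.9% | 4.6% |
| Slope, months 0, 3, 9 (wrong sign expected) | 7.7% | 11.6% |
| Baseline-to-week-12 change | 60.5% | 94.0% |

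**What week 12 can detect.** The smallest difference with 80% power is (1.960 + 0.842) × √(1/30 + 1/60) = 2.802 × 0.2236 = 0.63 SD. Adjusting for baseline with correlation 0.5 multiplies this by √0.75, giving 0.54 SD.

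**Regression to the mean.** Section 7.1 requires only one of PHQ9 ≥ 10, GAD7 ≥ 10, or trauma exposure with PCL5 ≥ 31. The protocol gives no means, SDs or correlations, so all are assumed: population PHQ9 mean 7 to 10, SD 5 to 5.5, test-retest correlation 0.6 to 0.8, GAD7 with the same mean and SD as PHQ9, the PCL5 criterion at one SD above its mean, and correlation between scales 0.5 to 0.7. Selecting on any one scale, with no treatment effect, simulated PHQ9 falls range from 0.43 (mean 10, SD 5, retest 0.8, between-scale 0.5) to 1.70 points (mean 7, SD 5, retest 0.6, between-scale 0.7). A paired test with n = 60 is significant in about 18% to 87% of trials. If everyone had to qualify on PHQ9 itself, the fall would be 0.8 to 2.4 points, but that is not the entry rule.

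**Endline timing.** Section 12 puts the intervention endline at 12 weeks after the first session, or within 14 days of completion, and the waitlist endline at 12 weeks after baseline. A participant finishing in 6 weeks could be assessed by about week 8 (6 weeks + 14 days) after starting, while the waitlist is assessed at a fixed 12 weeks.

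**The case against.** The strongest reply is that 15.3 does not specify a linear slope. It says regression will examine changes and, in a separate sentence, plot trends. A model with categorical time and arm-by-period terms, using week 12 for the waitlist, contains the valid contrast. Functional form is often left to a statistical analysis plan, which is not shown here. This stands. A reader might infer that the planned analysis cannot test the hypothesis at all; the document does not support that, because the baseline-to-week-12 data are collected in both arms. The wrong-sign result likewise belongs to one assumed layout of visits.

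A reader might also infer that the protocol will take within-arm improvement as proof of efficacy. No section says so. Section 4.1 names no group, and 3.2 introduces the waitlist design immediately before its expectation. These look like shortened forms of 15.1.

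Finally, this is a pilot sized for problem detection. That lowers the severity but does not remove the point: efficacy is the stated primary objective, testing is at two-sided 0.05, and 30 symptomatic people wait 12 weeks to supply the control.

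What survives does not depend on missing model detail. The three periods that the protocol does fix leave out, or dilute, its only randomised treated-versus-untreated comparison.

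**Conclusion.** The point holds in this form: 15.3 does not confine the between-arm test to baseline and week 12, and its 6-month period has no untreated comparator. This is so whether 6 months is counted from completion (Protocol Summary) or from endline (section 12).

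The size depends on how the trend is fitted. Under a single slope per arm and a maintained effect, the arm contrast is zero, nearly zero, or d/42 per month in the wrong direction. The week-12 contrast recovers d in full. Under a categorical-time model nothing need be lost, provided that the week-12 term is the one tested. The regression-to-the-mean figures rest wholly on assumed inputs and show only that within-arm change is not evidence of efficacy.

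This should be fixed before analysis. It does not invalidate the design or the data.

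**What to change.** - In 15.3, state that efficacy is the between-arm difference in PHQ9, GAD7 and PCL5 at the 12-week endline, using pre-crossover data only and adjusted for the baseline score.
- Reconcile the two endline definitions in section 12 so that both arms are compared at the same time from a common origin.
- Report the 1-, 3- and 6-month data as uncontrolled within-person change, with no efficacy test against the waitlist.
- Align the expectations in 3.2 and 4.1 with the comparison in 15.1.

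The analysis changes are rewording and need no new data. Reconciling the endline may shift when some assessments are taken. The price is that the 6-month result cannot be called controlled.

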| Title:        | Adaptation and assessment of a common element treatment approach designed to improve mental health in forcibly displaced individuals.                                                                                                                                                                                                                                                                                                                                                                                                                                                                                                                                                                                                                                                                                                                                                                                                                                                                                                                                                                                                                                                      |
| Population:   | 
Venezuelan migrants living in Lima (Peru), n = 90 (n = 60 in the intervention and n = 30 in waitlist control), of male and female biological sex, 18 years old or older, with depression (<math>\leq 10</math> in PHQ9), anxiety (<math>\leq 10</math> in GAD7) and/or post-traumatic stress disorder (history of trauma exposure, LEC 5 and <math>\leq 31</math> in PCL 5). Participants with suicidality, homicidality or psychosis will be excluded.
 
Lay-providers n = 10, of male and female biological sex, 18 years old or older, of any nationality.
                                                                                                                                                                                                                                                                                                                                                                                                                                                                                                                                                                                                                  |

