## 4.2 Study Outcome Measures

### 4.2.1 Primary Outcome Measures

Since the intervention is transdiagnostic and addresses several CMD, there will be three primary outcome measures. Changes in anxiety will be measured using the GAD7 scale. This is a 7-item instrument that measures generalized anxiety. Changes in depression will be assessed using the PHQ9 questionnaire, which is a 9-item instrument that measures depression. Both instruments have been chosen because they are short, easy to administer and have been widely used in research. Spanish versions of GAD7 and PHQ9 have been validated and used in Venezuelan and Peruvian populations. Furthermore, prior studies with this same population conducted by the main researcher have used these instruments. Regarding PTSD, changes will be measured using the PCL5 checklist which has been validated for its use in Spanish-speaking populations and utilized in research projects with similar populations. The LEC5, which identifies potentially traumatic events in the life course of the participants, will be used at baseline and in the follow-up assessments along with the PCL5.

The primary outcomes will be measured at baseline during screening and at endline 12 weeks after baseline in the case of waitlist control. In the intervention group, they will be assessed at baseline during screening, weekly (PCL5) or every two weeks (PHQ9 and GAD7) throughout the intervention before the next session, after the last session of the intervention and at 1-, 3-, and 6-month follow-ups after completion of the intervention. Participants will be sent a secure REDCap link, where they will be asked to answer each item of the instruments.

See appendix with the English and Spanish versions of the instruments.

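### Section 15.3 sets out to test whether sex modifies the treatment effect but names only stratification, which on its own does not compare the sexes; an interaction term should be named

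*Protocol*

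**What the plan says.** Protocol section 15.3 (Statistical Methods) sets the rule for sex: "All analyses will adjust for sex as a covariate and it will be tested as an effect modifier (e.g. stratification"). The same section fixes the error level: "All quantitative outcomes will be tested at two-sided" 0.05. It plans regression for changes in depression, anxiety and PTSD symptoms, and also for feasibility and acceptability measures.

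Section 4.2.1 says that "there will be three primary outcome measures": GAD7, PHQ9 and PCL5. Section 12 closes recruitment when "n = 90 is reached (n = 60 intervention; n = 30 waitlist control"). Section 2 admits both sexes but gives no expected mix. Section 5 allocates by random number and does not stratify by sex, so the stratification in 15.3 must mean stratified analysis. The protocol mentions no interaction term and no formal comparison between strata. It gives no target effect size or SD.

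**The concern.** The question in 15.3 has its own null hypothesis: the effect of intervention against waitlist is the same in men and women. An analysis within one sex addresses another null: no effect in that sex. Two within-sex analyses become a test of modification only when their estimates are set against each other, and the one example in the text stops short of that step.

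This matters because the strata are small. Ninety participants split by arm and by sex leave moderate power at best in each stratum, so two strata with the same true effect can easily fall on opposite sides of 0.05. An analyst who takes the example as the method could report that the intervention works in one sex and not in the other when the data show no such difference. With three primary outcomes, the opportunity arises three times.

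**Working it through.** **The plan's own figure.** Section 15.2 says that 59 participants "is sufficient to detect a problem that emerges for 5% of participants". Taking 95% confidence (the level is not stated), n = ln(0.05)/ln(0.95) = 58.4, rounded up to 59. The figure reproduces. It concerns problem detection and has no bearing on comparing the sexes.

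**Inputs.** From the protocol: 60 intervention, 30 waitlist, two-sided 0.05. Assumed, because the protocol gives neither: a standardised effect d that is equal in both sexes, and the share of participants of one sex. Also assumed: no dropout, and a two-sample t-test within each sex.

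**Formula.** With treated and control numbers n_T and n_C in a stratum, power p comes from the noncentral t distribution with n_T + n_C − 2 degrees of freedom and noncentrality d/√(1/n_T + 1/n_C). For sexes A and B:

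P(exactly one significant) = p_A(1 − p_B) + p_B(1 − p_A)

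**No effect in either sex.** 2 × 0.05 × 0.95 = 9.5%, whatever the sex split.

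**Sexes 50:50** (30 against 15 in each sex)

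| d | power in each sex | exactly one significant |
|---|---|---|
| 0.3 | 0.153 | 25.9% |
| 0.5 | 0.340 | 44.9% |
| 0.8 | 0.696 | 42.3% |
| 1.2 | 0.960 | 7.7% |

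**Sexes 70:30** (42 against 21, and 18 against 9)

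| d | power, larger sex | power, smaller sex | exactly one significant |
|---|---|---|---|
| 0.3 | 0.197 | 0.109 | 26.3% |
| 0.5 | 0.453 | 0.218 | 47.3% |
| 0.7 | 0.732 | 0.378 | 55.7% |
| 0.8 | 0.838 | 0.470 | 52.0% |

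For example, 0.732 × 0.622 + 0.378 × 0.268 = 0.557. For d from 0.3 to 0.8 and 50 to 70% of one sex, the range is therefore about 26 to 56%.

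**Wider inputs.** At 60:30, with d from 0 to 1.2 and splits up to 80:20, the range runs from 7.7% (d = 1.2, 50:50) to about 64% (63.8% at d = 0.7, 80:20).

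**Sensitivity.** Section 5 says: "Participant with odd numbers will be assigned to the active treatment group and participants with even numbers to the waitlist control group". Taken literally this gives about 45:45. The range is then 28 to 55% over d = 0.3 to 0.8 and splits from 50:50 to 70:30, although at d = 1.2 with equal sexes it falls to 4.7%. With 20% dropout (48:24) it is 23 to 56%.

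**Interaction test.** In 20,000 simulated trials per setting with equal effects, the treatment-by-sex test rejected in 4.9 to 5.1%, whatever the size of the common effect. Its precision, with share q of one sex:

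SE = √[(1/60 + 1/30) × (1/q + 1/(1 − q))] = √[0.05/(q(1 − q))]

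- q = 0.5: SE 0.447 SD, 95% half-width 1.96 × 0.447 = 0.88 SD
- q = 0.7: SE 0.488 SD, 95% half-width 1.96 × 0.488 = 0.96 SD

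| true difference between sexes | power, 50:50 | power, 70:30 |
|---|---|---|
| 0.5 SD | 20% | 17% |
| 0.8 SD | 42% | 37% |
| 1.0 SD | 60% | 53% |

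**The case against.** The strongest reply is that the protocol asks the right question and offers stratification only as an example. A reader might infer that the trial will run a test in each sex and compare the p-values. The text does not say that. Stratum estimates can be compared formally, and an analysis plan not shown here may specify an interaction term. This stands: the percentages above describe a decision rule that the wording permits, not one that it states. What remains is that the protocol commits to a test and illustrates it with a method that does not supply one. That is a weak choice in the text itself, not merely detail left for later.

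A reader might also take 26 to 56% as a fixed property of the design. It is not. It depends on an effect size and a sex mix that the protocol does not give, and equal effects include no effect at all, where the figure is 9.5%. The planned regression may also have different power from a plain t-test. That changes the percentage, not the mechanism.

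A further inference would carry the point over to section 15.1: "Experiences in migration, integration and demographic variables may moderate the efficacy of the intervention". That sentence names no method and states nothing wrong. Any complaint there would rest on absent detail alone, so it is not part of this point.

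Finally, this is a pilot sized for problem detection, moderation by demographic variables is an exploratory objective (section 4.1), and an interaction test will seldom be decisive at 90 participants. All true. This limits the weight of the point, and it is the reason for the exploratory label.

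**Conclusion.** The point holds in a limited form. Section 15.3 promises a test of effect modification by sex, and its only example does not by itself provide one. If within-sex significance were used in its place, the chance of an apparent sex difference under equal effects would be 9.5% with no effect. It would be about 26 to 56% for a common effect of 0.3 to 0.8 SD with 50 to 70% of one sex, and about 8 to 64% over the wider inputs tried at 60:30. An interaction test holds about 5%. All of these except the no-effect figure and the size of the interaction test rest on assumed effect sizes and sex splits. The change is worth making because it costs little, but it concerns a secondary question in a pilot and does not touch the main comparison between arms.

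**What to change.** In section 15.3, delete the parenthetical example that closes the sentence on sex and add:

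> For PHQ9, GAD7 and PCL5, effect modification by sex will be assessed by a treatment-by-sex interaction term in the regression comparing the randomised arms at endline, before the waitlist group is treated. It will be reported with its 95% confidence interval and labelled exploratory. Sex-specific estimates with confidence intervals will be shown descriptively. A difference in significance between the sexes will not be read as evidence that the effects differ, and a non-significant interaction will not be read as evidence that they are equal.

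The restriction to the three symptom scales is deliberate. Attendance and session acceptability have no waitlist counterpart before that group is treated, so a treatment-by-sex term is undefined for them. Endline is used because the waitlist group receives the intervention afterwards. The wording does not settle when endline falls in the intervention arm. Sections 2, 4.2.1 and 12 describe that differently and need to be reconciled separately.

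The cost is a few sentences and one model term, with no new data or participants. The downside is an openly imprecise estimate: a 95% interval of about ±0.88 to ±0.96 SD, and about 20% power for a 0.5 SD difference.
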